## Abstract

**Background:**

Major depressive disorder is a severe, recurrent and disabling condition. Although diagnosis and clinical monitoring are based on medical interviews and validated rating scales, voice and speech analysis may provide complementary digital biomarkers reflecting depressive severity and clinical evolution. However, current evidence remains limited by methodological heterogeneity, predominantly cross-sectional designs, limited longitudinal data and underrepresentation of non-English-speaking clinical populations.

**Objective:**

The aim of the VOICE-DEP study is to develop and formalize a standardized, reproducible and clinically grounded protocol for the multimodal analysis of voice and speech during medical interviews as a tool to support the diagnosis of depressive disorder and to assess whether speech-derived digital biomarkers change over time in parallel with clinical severity measures.

**Methods:**

VOICE-DEP is an observational, prospective, longitudinal pilot study of patients with major depressive disorder with a healthy control group, conducted in a hospital-based clinical setting in Spain. The study will include 25 adult patients with moderate or severe unipolar depression, with or without psychotic symptoms, and 50 healthy controls without a personal history of psychiatric disorders. Patients will be assessed at five time points: baseline (V0) and four monthly follow-up visits at 30, 60, 90 and 120 days. Healthy controls will be assessed once at baseline. The planned dataset comprises 175 voice recordings: 125 from patients and 50 from controls. At each assessment, the Montgomery-Asberg Depression Rating Scale related part of the medical interview, lasting approximately 10–30 minutes and including an initial free-speech segment, will be recorded using a standardized audio protocol. Acoustic (e.g., pitch, intensity), paralinguistic (e.g., speed rate, prosodic range) and linguistic (e.g., sentiment polarity, lexical diversity) features will be extracted and analyzed in relation to clinician-rated severity measures and self-reported symptoms.

**Expected outcomes:**

This protocol is expected to generate a clinically grounded Spanish-language longitudinal speech corpus and a transparent analytical framework for evaluating voice- and speech-derived digital biomarkers as complementary tools for depression assessment and monitoring.

## 1. Introduction

Major depressive disorder (MDD) is one of the leading contributors to global disability, affecting more than 280 million people worldwide and constituting a major public health challenge [1]. Despite decades of research, clinical assessment and monitoring of depression still rely predominantly on structured interviews and rating scales, which are inherently subjective and susceptible to recall bias and inter-rater variability [2,3].

In recent years, the identification of objective, scalable and non-invasive digital biomarkers has become a central goal of precision psychiatry [4]. Among behavioral signals, human speech has emerged as a promising source of information because speech production integrates motor control, cognition, affective regulation and autonomic function [5]. Alterations in prosody, speech rate, pauses, intensity and voice quality have been consistently associated with depressive states [6,7].

Recent advances in artificial intelligence have accelerated research on voice-based depression assessment. Machine learning, natural language processing and large language models have shown promising results using acoustic, paralinguistic and linguistic features extracted from speech recordings [8,9]. In parallel, recent studies have increasingly adopted multimodal approaches integrating audio and text information. Representative studies in the field are summarized in Table 1.

**Table 1 pone.0353827.t001:** Representative state-of-the-art studies in voice-based depression research.

Reference	Design and Dataset	Sample (N)
Jin et al., 2026 [10]	Cross-sectional; MMPsy adolescent dataset (text + audio, PHQ-9).	1275 participants
Li et al., 2025 [11]	Cross-sectional; AVEC2013 and AVEC2014 speech datasets (BDI-II).	84 participants (150 clips)
Xu et al., 2025 [12]	Cross-sectional; CMDC and DAIC-WOZ multimodal datasets (voice + text, PHQ-8).	234 participants
Ali et al., 2025 [13]	Longitudinal; DEW dataset (multimodal speech).	Not reported
Mazur et al., 2025 [14]	Cross-sectional; remote personal devices.	14,898 participants
Zhang et al., 2024 [9]	Cross-sectional; DAIC-WOZ dataset (text + acoustic landmarks).	189 interviews
Ghosh et al., 2024 [15]	Cross-sectional controlled; DAIC-WOZ.	189 participants
Huang et al., 2024 [16]	Cross-sectional controlled; DAIC-WOZ.	189 participants
Sadeghi et al., 2024 [17]	Cross-sectional; E-DAIC dataset (text + facial features, PHQ-8).	275 interviews
Anand et al., 2024 [18]	Cross-sectional; E-DAIC dataset (text, audio and visual; PHQ-8).	275 interviews
Menne et al., 2024 [19]	Cross-sectional; clinical cohort using speech tasks (BDI-II/ HAMD).	96 participants
Ronneberg et al., 2024 [20]	RCT-controlled; voice-based AI coaching.	200 participants
Wu et al., 2023 [8]	Cross-sectional; DAIC-WOZ dataset using SSL speech representations.	189 interviews
Cansel et al., 2023 [21]	Cross-sectional controlled; smartphone-based recordings.	104 participants
Berardi et al., 2023 [22]	Cross-sectional controlled; digital voice recorder.	60 participants
Li et al., 2023 [23]	Cross-sectional; clinical interviews with NLP-based analysis.	329 participants
Kim et al., 2023 [24]	Cross-sectional controlled; smartphone-based recordings.	318 participants
Wasserzug et al., 2023 [25]	Cross-sectional controlled; mobile phone recordings.	144 participants

HC = Healthy Controls; MDD = Major Depressive Disorder; SZ = Schizophrenia; BD = Bipolar Disorder; ANX = Anxiety Disorder; RCT = Randomized Controlled Trial; LLM = Large Language Model; SSL = Self-Supervised Learning; NLP = Natural.

However, systematic reviews continue to highlight substantial methodological heterogeneity across this literature [26]. Differences in recording conditions, speech tasks, feature extraction pipelines, validation strategies and clinical reference standards limit reproducibility and comparability across studies. Moreover, the current literature remains dominated by cross-sectional designs and English-speaking datasets, while longitudinal studies in clinically characterized Spanish-speaking populations remain scarce.

Another important limitation is that many studies rely primarily on self-report questionnaires as reference labels for model training and evaluation. In contrast, clinician-rated instruments such as the Montgomery–Asberg Depression Rating Scale (MADRS) may provide a complementary, clinically grounded severity reference given its demonstrated validity and inter-rater reliability [27]. Longitudinal designs are also particularly relevant because they allow evaluation of whether speech-derived digital biomarkers evolve in parallel with changes in depressive severity over time [28].

Recent evidence in Spanish-speaking clinical populations further supports the relevance of integrating linguistic information into speech-based depression assessment [29]. Nevertheless, important challenges remain unresolved, including the standardization of recording conditions, harmonization of clinical anchors, definition of speech elicitation procedures and longitudinal evaluation of within-subject changes. These limitations highlight the need for transparent and reproducible protocol-driven studies designed specifically for clinical translation.

The present study protocol addresses these challenges by proposing a longitudinal, hospital-based framework for the collection and analysis of speech data in Spanish-speaking patients with depressive disorder and healthy controls. By integrating acoustic, paralinguistic and linguistic features and anchoring them to validated clinician-administered scales, the VOICE-DEP study aims to advance voice-based depression research toward clinically interpretable and reproducible methodology.

## 2. Materials and methods

### 2.1. Aim of the study, design and setting

The overall aim of the VOICE-DEP study is to develop and formalize a standardized, reproducible and clinically grounded protocol for the multimodal analysis of voice and speech during medical interviews as a tool to support the diagnosis and longitudinal monitoring of depressive disorder.

The working hypothesis is that major depressive disorder and its clinical evolution are associated with changes in acoustic, paralinguistic and linguistic characteristics of voice and speech, and that these changes can be analyzed in a standardized and reproducible manner in a routine clinical setting.

**Primary objective.** The primary objective is to establish a reproducible clinical framework for extracting and analyzing acoustic, paralinguistic and linguistic features from semi-structured medical interviews, allowing discrimination between patients with a medical diagnosis of depressive disorder and healthy controls using voice-based models anchored to validated clinician-rated clinical reference standards.

**Secondary objectives.** The secondary objectives are: i) To construct a longitudinal Spanish-language clinical speech corpus including repeated voice recordings from patients with depressive disorder and single-session recordings from healthy controls; ii) To characterize the association between speech-derived digital biomarkers and clinician-rated measures of depressive severity, including their evolution over time; iii) To evaluate the added value of multimodal models combining acoustic, paralinguistic and linguistic features compared with unimodal models; iv) To assess intra-individual vocal changes across repeated assessments and their association with changes in clinical severity; v) To provide a transparent methodological framework that may facilitate replication, cross-study comparison and future external validation in other clinical presentations, diagnoses, languages and sociocultural settings; vi) To explore whether specific treatment modalities are associated with greater changes in voice and speech in parallel with clinical evolution.

**Study design and setting.** This is an observational, prospective, longitudinal pilot study with a healthy control group. The study will be conducted in a hospital-based clinical setting, including both outpatient consultations and inpatient care at the Department of Psychiatry of a university hospital. The expected study duration is 24 months.

### 2.2. Study population and participant characteristics

The study will include two groups: (1) patients with a medical diagnosis of moderate or severe unipolar depression and (2) healthy control participants without a personal history of depression or any other psychiatric disorder.

Inclusion criteria for patients are: Age 18 years or older; Native Spanish speakers or individuals with sufficient fluency in Spanish to maintain a clinical interview; Capacity to understand study procedures and provide written informed consent, according to the investigator’s judgement; Medical diagnosis of moderate or severe unipolar depression, with or without psychotic symptoms, according to ICD-10 categories: moderate depressive episode (F32.1), severe depressive episode without psychotic symptoms (F32.2), severe depressive episode with psychotic symptoms (F32.3), recurrent depressive disorder, current episode moderate (F33.1), recurrent depressive disorder, current episode severe without psychotic symptoms (F33.2), or recurrent depressive disorder, current episode severe with psychotic symptoms (F33.3), regardless of whether the patient receives psychotherapeutic, pharmacological or neurostimulation treatment, or chooses not to receive active treatment while remaining under clinical follow-up.

Exclusion criteria for patients are: Severe neurological disorders affecting speech production or cognitive function, such as severe dementia; Severe voice or speech disorders unrelated to depression that prevent completion of the clinical interview through verbal language; State of intoxication due to substance use at the time of assessment; Other severe medical conditions interfering with study participation or speech production.

Inclusion criteria for healthy controls are: Age 18 years or older. Exclusion criteria for healthy controls are: Personal history of depression or any other psychiatric disorder; Severe neurological disorders affecting speech production or cognitive function, such as severe dementia; Severe voice or speech disorders unrelated to depression that prevent completion of the clinical interview through verbal language; State of intoxication due to substance use at the time of assessment; Other severe medical conditions interfering with study participation or speech production.

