Although a balanced baseline comparison between patients and healthy controls would be methodologically desirable, the final allocation was defined according to feasibility considerations. Healthy controls will be individually matched to patients by age and sex whenever feasible. If individual matching cannot be achieved, control recruitment will be guided by the age and sex distribution of the patient group to obtain group-level frequency matching as closely as possible. Recruitment of clinically characterized patients with moderate or severe depressive disorder is expected to be more demanding because it requires repeated clinical assessments and longitudinal follow-up. In contrast, healthy controls require only a single baseline visit, allowing the inclusion of a larger control group without substantially increasing study burden. Therefore, the study will include 25 patients and 50 healthy controls. This design is expected to strengthen the baseline characterization of non-depressed speech patterns while preserving the longitudinal focus of the clinical cohort.

At participant level, baseline analyses will compare patients and healthy controls, whereas longitudinal analyses will focus on within-patient changes across repeated assessments. For predictive modeling, the imbalance between groups will be explicitly considered through appropriate analytical strategies, such as participant-level data splitting, balanced resampling, class weighting or sensitivity analyses when applicable.

Given the pilot nature of the study and the moderate sample size, classifier performance estimates will be interpreted as exploratory and hypothesis-generating. The study will prioritize transparent feature extraction, reproducible preprocessing, clinically interpretable modeling and longitudinal within-subject analysis over the development of a definitive deployable diagnostic model. Model complexity will be limited in relation to the available sample size, and classifier performance estimates will be accompanied by confidence intervals whenever feasible.

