### 2.6. Variables

All study variables will be recorded in a pseudonymized case report form developed specifically for the VOICE-DEP study. Variables will be classified into: (i) baseline variables collected only at V0, and (ii) longitudinal visit variables collected at V0, V1, V2, V3 and V4 in patients with depressive disorder.

Exposure variable: The main exposure variable is the medical diagnosis of moderate or severe unipolar depressive disorder, with or without psychotic symptoms, according to the predefined ICD-10 categories included in the protocol.

Primary outcome variables: The primary outcome variables are the standardized voice recording and the multimodal speech- and speech-derived variables extracted from the recorded clinical interview. These variables will be grouped into acoustic, paralinguistic and linguistic domains.

Clinician-rated and self-reported symptom variables: At each study visit, depressive symptom severity and global clinical status will be assessed concurrently with the voice recording using the MADRS, the Clinical Global Impression scale (CGI), and the Patient Health Questionnaire-9 (PHQ-9). These variables will provide the clinical reference outcomes for cross-sectional and longitudinal analyses. Psychotic depression, operationally defined by an ICD-10 diagnosis of F32.3 or F33.3, will be recorded as a binary clinical variable. The same clinician-rated and self-reported assessments will also be conducted in healthy controls at baseline (V0) to identify possible subthreshold symptoms.

Baseline and longitudinal variables: Baseline variables collected at V0 will include demographic, anthropometric, clinical and contextual information, including psychiatric and medical history, substance use, stressful life events, and previous depressive episodes. Longitudinal variables collected across visits will include recording traceability variables, symptom scales, pharmacological treatment variables, psychotherapy variables and neurostimulation-related variables.

Metadata related to the recording process, including pseudonymized audio identifiers and recording incidents, will also be documented for traceability and quality control purposes.

The complete list of study variables operationalized in the VOICE-DEP case report form is summarized in Table 2. The list of multimodal voice- and speech-derived variables is summarized in Table 3.

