**Table 2 pone.0353827.t002:** Study variables recorded in the VOICE-DEP case report form and assessment schedule.

Domain	Description	Assessment visits
Participant identification	Participant category (patient or control), study code, and visit date	V0–V4 in patients; V0 in controls
Sociodemographic and anthropometric baseline variables	Sex, age, marital status, place of residence, birth order in the sibship, height, weight, body mass index, body surface area, educational level, childcare responsibilities, caregiving responsibilities for dependent relatives, religious belief, community religious practice, and social relationships	V0 only
Lifestyle, family history and contextual baseline variables	First-degree family psychiatric history, toxic habits, tobacco, alcohol, cannabis, cocaine, amphetamine and other substance use, physical activity, diet pattern, complementary or alternative treatments and specific prescribed diets, pharmacogenetic or pharmacodynamic isoform information when available, employment status, night work, acute and chronic stressful life events, and current and lifetime traumatic events	V0 only
Clinical baseline variables	Principal diagnosis according to ICD-10 depressive categories, psychiatric comorbidities, medical comorbidities, previous suicidal ideation, previous suicidal behavior, previous self-harm, duration of the current episode, time since initial diagnosis, and number of previous depressive episodes	V0 only
Recording and audio traceability variables	Whether the voice recording was obtained, pseudonymized audio file identifier, presence of recording incidents, and type of incident (patient need, clinical need, technical problem, others)	V0–V4 in patients; V0 in controls
Clinician-rated and self-reported symptom variables	Depressive symptom severity assessed with MADRS, global clinical impression assessed with CGI, and self-reported depressive symptom burden assessed with PHQ-9	V0–V4 in patients; V0 in controls
Pharmacological treatment variables	Pharmacological treatment received, including total daily dose in mg/24h, dosing interval, administration time, and duration of treatment at the recorded dose	V0–V4 in patients
Non-pharmacological treatment and psy-chotherapy variables	Sleep hygiene measures, diet pattern, regular physical activity, discontinuation of toxic habits, psychotherapy attendance, psychotherapy type, and psychotherapy frequency	V0–V4 in patients

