### 2.7. Statistical and analytical plan

The analytical strategy of the VOICE-DEP study is designed to support the primary and secondary objectives of the protocol while ensuring methodological transparency, reproducibility, and robustness. In accordance with the study design, the analysis will address three complementary dimensions: (i) descriptive characterization of the study sample and extracted variables, (ii) exploratory cross-sectional association and discrimination analyses between patients with depressive disorder and healthy controls, and (iii) longitudinal intra-individual modeling of changes in voice- and speech-derived variables in relation to clinical evolution.

First, a descriptive analysis will be performed for all study variables recorded in the case report form. Quantitative variables, including acoustic, paralinguistic, and linguistic features, will be summarized using means and standard deviations or medians and interquartile ranges, as appropriate according to their distribution. Qualitative variables will be described using absolute frequencies and percentages. This descriptive phase will include both baseline variables collected at V0 and longitudinal variables collected across repeated visits in patients. Age, sex, educational level and available socioeconomic-related variables will be compared between groups and considered as covariates in adjusted or sensitivity analyses when relevant imbalance is observed and the sample size permits stable estimation.

Second, the association between continuous voice- and speech-derived digital biomarkers and clinical severity measures will be explored using Pearson or Spearman correlation coefficients, depending on distributional assumptions. These analyses will focus on the relationship between multimodal voice-derived variables and clinician-rated depressive symptom severity measured with the MADRS, global clinical status measured with the CGI, and self-reported depressive symptom burden measured with the Patient Health Questionnaire-9 (PHQ-9).

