The study is conducted in a single clinical center and focuses on Spanish-speaking participants, which may induce selection bias and restrict external validity across healthcare systems, dialects, or linguistic contexts. Dialectal variation across Spanish-speaking regions may influence acoustic, prosodic, and linguistic characteristics. Therefore, the findings will be interpreted within the linguistic and geographical context of the study population and will require future external validation in samples from other Spanish-speaking regions and sociolinguistic settings. However, this focus also addresses a relevant gap in the literature, which has been predominantly centered on English-language datasets.

Because of the observational design and treatment heterogeneity, changes in speech cannot be fully disentangled from the effects of specific treatments. Treatment-related analyses will therefore remain exploratory and will not support causal inference.

Residual variability related to the recording time of the day will be acknowledged as a study limitation.

Finally, clinician-administered scales are used as the primary reference standards, but they are themselves subject to measurement variability and do not constitute an objective ground truth. In addition, symptom-focused MADRS questions may influence some linguistic variables, particularly sentiment-related measures, which will therefore be interpreted cautiously. The present protocol does not aim to replace clinical judgment but rather to complement it by identifying speech-derived markers that correlate with established measures of depressive severity.

In summary, the formal clinical diagnosis will define the study groups, whereas the MADRS, CGI, and PHQ-9 will be used to quantify symptom severity and longitudinal change. Speech-derived measures will therefore be interpreted as complementary correlates of clinical assessment rather than as independent objective standards, under the premise of supporting, but not replacing, the clinical judgment.

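### Native language is not a control criterion, a listed CRF variable, a matching factor or a covariate, so an unmeasured native/non-native imbalance could bias the patient-control speech comparison

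*Protocol article*

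**What the plan says.** Section 2.2 lists eligibility for the two groups one after the other. Patients must be "Native Spanish speakers or individuals with sufficient fluency in Spanish to maintain a clinical interview". For controls the text reads "Inclusion criteria for healthy controls are: Age 18 years or older". The nearest control exclusion is "Severe voice or speech disorders unrelated to depression that prevent completion of the clinical interview through verbal language", which concerns pathology and not command of the language.

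Section 2.6 states: "The complete list of study variables operationalized in the VOICE-DEP case report form is summarized in Table 2". The sociodemographic row of Table 2 begins "Sex, age, marital status, place of residence, birth order in the sibship, height, weight, body mass index, body surface area, educational level" and goes on to items such as religious practice and social relationships. No row names native language, fluency, country of birth or variety of Spanish.

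On comparability, Section 2.4 says "Healthy controls will be individually matched to patients by age and sex whenever feasible", with frequency matching on the same two factors as the fallback. Section 2.7 says "Age, sex, educational level and available socioeconomic-related variables will be compared between groups and considered as covariates", subject to observed imbalance and sample size.

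Section 3.1 concedes: "Dialectal variation across Spanish-speaking regions may influence acoustic, prosodic, and linguistic characteristics". It treats this as a limit on generalisation and does not raise it as a possible difference between the two groups.

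**The concern.** The primary objective in Section 2.1 includes discriminating patients from controls by acoustic, paralinguistic and linguistic features. Many of the features in Table 3 can plausibly differ between native and non-native speakers whatever their mood: speech rate, pauses, lexical diversity, sentence length, coherence, prosodic range and formants.

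The groups also arrive by different routes. Patients are recruited consecutively by physicians in routine care, and controls are invited by the research team (Sections 2.3 and 2.4). Nothing in the design makes their language backgrounds alike. If the non-native shares differ, part of the feature difference, and part of what a classifier learns, would reflect language background and be read as depression. The bias could run either way, creating a difference or hiding one.

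A later analysis plan can adjust only for what was collected. False discovery rate control, which Section 2.7 provides, deals with chance findings and does not remove a systematic shift.

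**Working it through.** **1. The text, side by side**

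| Stage | Patients | Controls | Language handled? |
|---|---|---|---|
| Inclusion (2.2) | Native or sufficiently fluent in Spanish | Adult age | Patients only |
| Exclusion (2.2) | Speech pathology and others | Same, plus psychiatric history | No |
| CRF list (Table 2) | Residence, education and others | Same baseline fields | No |
| Matching (2.4) | – | Age and sex | No |
| Covariates (2.7) | Age, sex, education, socioeconomic | Same | No |

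The patient criterion itself admits fluent non-native speakers. Copying it to controls would make eligibility symmetric but would not equalise the native/non-native mix. The mix has to be recorded as well.

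**2. The plan's own figure**

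Inputs from Section 2.4: 25 patients, 50 controls, two-sided 0.05, 80% power, stated detectable d of about 0.70.

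- Normal approximation: d = (1.960 + 0.842) × √(1/25 + 1/50) = 2.802 × 0.245 = 0.686.
- Two-sample t-test (noncentral t): d = 0.695.

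The stated figure reproduces, and this point does not alter it. It serves only as a yardstick.

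**3. Size of a possible bias**

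Neither input below is in the documents. Both are assumptions, shown as ranges.

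- Shift of a feature between native and non-native speakers: 0.5 to 1.0 SD.
- Difference in non-native share between groups: 10 to 20 percentage points. That is 2.5 to 5 of 25 patients, or 5 to 10 of 50 controls, if the other group has none.

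Bias in the group contrast = shift × difference in share:

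- lowest: 0.5 × 0.10 = 0.05 SD
- highest: 1.0 × 0.20 = 0.20 SD

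Against 0.70 this is 0.05/0.70 = 7% to 0.20/0.70 = 29%.

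With standard error √(1/25 + 1/50) = 0.245, the chance that a feature unrelated to depression reaches two-sided p < 0.05 is 1 − Φ(1.96 − b/0.245) + Φ(−1.96 − b/0.245):

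- b = 0.05: about 5.5%
- b = 0.10: about 6.9%
- b = 0.20: about 12.9%

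The nominal rate is 5%. The effect on one feature is modest, but the same imbalance would act on many language-dependent features at once.

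**4. Price of a native-only analysis**

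Under the upper assumption, excluding non-native speakers removes 5 patients or 10 controls:

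- 20 against 50: 2.802 × √(1/20 + 1/50) = 0.741
- 25 against 40: 2.802 × √(1/25 + 1/40) = 0.714

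Both compare with 0.686 for the full sample by the same approximation.

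**The case against.** The strongest reply is that the missing control criterion matters little in practice. Controls must follow the study information, consent, and complete the clinical and MADRS interviews and the PHQ-9. Their recordings enter a corpus that Section 2.1 calls Spanish-language, and Section 3.1 describes the participants as Spanish-speaking. A reader might infer from Section 2.2 that people with little Spanish could be enrolled as controls. The rest of the protocol makes that unlikely, and this point does not rest on it.

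Second, Table 2 is a summary. Recording time, valid-speech duration and word count are to be documented under Section 2.5, yet Table 2 names none of them. Absence from the table therefore does not prove absence from the CRF. This stands as a caution, but Section 2.6 presents the list as complete, and neither the matching nor the covariate text mentions language either.

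Third, a reader might conclude that data on participants already enrolled are lost. They are not. Native language is a fixed trait, data are pseudonymised, patients return for four visits, and consent covers access to clinical records. Controls attend once, so backfilling takes more effort for them, but it can be done.

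Fourth, the comparison is labelled exploratory (Sections 2.4 and 2.7), education and residence are recorded, and Section 3.1 restricts interpretation to the study's linguistic setting. This lowers the stakes. None of it would reveal a difference in native language between the groups.

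Finally, details of a sensitivity analysis are often left to an analysis plan. That is fair, but the analysis depends on a variable that must be collected at entry.

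**Conclusion.** The point holds in a limited form. The language criterion is stated for one group only, and native language is not among the listed CRF variables, matching factors or covariates. What follows is a possible, unmeasured imbalance in native versus non-native status. It bears on the exploratory patient-control comparison of linguistic, prosodic and some acoustic features. Within-patient longitudinal analyses are largely unaffected, because native language does not change within a person.

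The 0.05 to 0.20 SD range rests wholly on the assumed shift of 0.5 to 1.0 SD and the assumed 10 to 20 point difference in share. It shows what could happen. The documents contain no evidence that the groups do differ, or in which direction, and a 1 SD shift would not be expected for every feature. The study is not invalidated. The gap is worth closing because closing it is cheap and recruitment, open since 21 May 2026, is planned to run to December 2027.

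**What to change.** - State for controls in Section 2.2 the same Spanish-language criterion that patients have. Alone this corrects only the asymmetry.
- Record native language at V0 for every participant, name it in Table 2, and backfill it for those already enrolled. If the full CRF already holds the field, adding it to Table 2 is enough. Variety of Spanish is an optional second field; it would put data behind the dialect caveat in Section 3.1.
- Report native language by group with the other baseline comparisons in Section 2.7, and specify a native-speakers-only sensitivity analysis of the patient-control comparison.

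The cost is a short amendment by the route in Section 3.3, one CRF field, some effort to reach controls already seen, and a slightly smaller sample in the sensitivity analysis. Under the upper assumption used above, the detectable difference there rises from 0.686 to between 0.714 and 0.741. The main analysis keeps its full sample, and control recruitment should hardly change.
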